### Sample size

For our primary outcome, we aim to detect a reduction in inappropriate psychotropic drug prescribing of 5 points minimum (standard deviation = 15) on the APID index from the baseline to the final measurement (16 months) [23, 71]. We expect that APID values will be nested within NHs, the main level of randomization in our design. Assuming an average size of 25 residents per NH, a power of 0.80, a significance level (alpha) of 0.05, we will need 284 psychotropic drug users. Given the multilevel design with two measurements after baseline, we anticipate that we will then need to increase this to a sample size of 364 (15 clusters) for an intraclass correlation coefficient of 0.1 [44] and a calculated design factor of 1.28 (the factor at which the original N has to multiplied). To allow for a cluster dropout of about 10% [72], and to obtain an even number of clusters, we plan to include 16 clusters with 364 residents in total. Given that approximately 60% of residents with dementia will be prescribed psychotropic drugs [20], this number will need to be further increased to 607 residents. Previous studies have shown that we can also anticipate a loss to follow-up of about 30% per year [5], which would amount to 40% in the 16 months in our study. However, in the event a resident dies or moves away from the unit, we will enroll the newly admitted resident, precluding the need to account further for attrition. Consequently, the case mix during our study will vary, and information from dropouts will need to be included in an intention to treat analysis.

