Analyses will be adjusted for baseline outcome values (e.g., inappropriate psychotropic drug prescribing and NPS), time, and confounders (e.g., cognitive abilities, as measured with the CPS, type of dementia, distress in nurses due to NPS). We will adjust for factors that could explain why an intervention did not succeed at the team level (e.g., staff attitudes toward the use of new interventions or treatments, as measured by the EBPAS, and the cooperation between staff members, the working conditions and characteristics of the DSCU, as measured by the CVF scale). Possible interaction effects of the intervention with time and with an NH will also be investigated. Sensitivity analyses will be used to examine differences between NHs with respect to extent of performance, considering whether degree of implementation (such as more coaching) is associated with a greater reduction of inappropriate prescribing or whether attitude serves as an effect modifier. When indicated, subgroup analyses will be used to consider NHs that implement their plans unsuccessfully and NHs that implement their plans successfully. We will also conduct a missing value analysis to evaluate whether missing data are likely to be missing at random, and we will consider replacement if appropriate. Normal probability plots and plots of standardized residuals versus predicted values will be inspected to assess whether the assumptions of normality and homogeneity of variance are met. In the event of noncompliance, data transformation will be considered. The double ratings of QoL and health status, as perceived by nursing staff and family members, will be analyzed separately. Data from the process evaluation interviews will be examined in the content analysis and any barriers and facilitators will be analyzed according to the Consolidated Framework For Implementation Research [74].

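### Adjusting for the baseline outcome value conflicts with relying on replacement residents to cover attrition: about 30% of planned follow-up records would not contribute unless values are imputed

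*Protocol article*

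**What the plan says.** Three statements in the Protocol article bear on this.

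- **Sample size, attrition.** About 30% loss per year is expected, put at 40% over 16 months. No inflation follows, on one stated ground: "we will enroll the newly admitted resident, precluding the need to account further for attrition".
- **Sample size, dropouts.** The section accepts that case mix will vary and adds that "information from dropouts will need to be included in an intention to treat analysis".
- **Data analysis.** A multilevel model handles the repeated measurements and the clustering, and "Analyses will be adjusted for baseline outcome values (e.g., inappropriate psychotropic drug prescribing and NPS), time, and confounders". A missing value analysis is planned, and replacement of missing values will be considered where appropriate.

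Measurements are taken at 0, 8 and 16 months (Design and eligibility). The article does not define a baseline value for a resident who enters after month 0.

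**The concern.** Replacement enrolment protects the sample size only if the replacements enter the analysis. A resident admitted after month 0 has no month-0 APID score. If that score is a covariate, the resident has no complete row. A resident who leaves before 8 months has the opposite problem: the covariate is present, but there is no outcome for it to predict. A model with baseline as covariate therefore uses neither group unless values are imputed.

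Three things are at stake: the only reason given for not allowing for attrition, the intention-to-treat statement, and the analysis set. That set would become residents present at month 0 and again at 8 months or later. The intervention is aimed at the unit, so dropping newcomers omits residents whose prescribing it is meant to change.

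**Working it through.** **1. The plan's own figures.** Inputs from Sample size: "reduction in inappropriate psychotropic drug prescribing of 5 points minimum (standard deviation = 15) on the APID index"; "a power of 0.80, a significance level (alpha) of 0.05, we will need 284 psychotropic drug users"; "Assuming an average size of 25 residents per NH"; "for an intraclass correlation coefficient of 0.1 [44] and a calculated design factor of 1.28"; "we plan to include 16 clusters with 364 residents in total".

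- Per arm: 2 × (1.960 + 0.842)² × 15² / 5² = 141.3, so 142; total 284. Reproduced (two-sided alpha).
- Stepped-wedge design effect: [1 + ρ(ktn + bn − 1)] / [1 + ρ(ktn/2 + bn − 1)] × 3(1 − ρ) / [2t(k − 1/k)], with k = 2 steps, t = 1 measurement per step, b = 1 baseline measurement, n = 25, ρ = 0.1. This is (8.4 / 5.9) × 0.9 = 1.281. Reproduced.
- 284 × 1.28 = 363.5, so 364 users; 364 / 0.60 = 606.7, so 607 residents. Reproduced.

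The value b = 1 means that month 0 is counted as an outcome measurement. The sample size thus rests on a model in which month 0 is an outcome, while the Data analysis text makes it an adjustment variable.

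**2. Records without their own month-0 value.** With a constant census of 364 users, 2 × 364 = 728 follow-up records are planned.

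| Loss at 30% per year | Original users at 8 months | At 16 months | Records with a month-0 value | Records without |
|---|---|---|---|---|
| Compounding (0.7^(8/12) = 0.788; 0.7^(16/12) = 0.622) | 287 | 226 | 513 (70%) | 215 |
| Linear, as in the article (20%; 40%) | 291 | 218 | 510 (70%) | 218 |

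In addition, 77 (compounding) or 73 (linear) original users leave before 8 months with a baseline value and no follow-up.

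**3. Effect on precision.** This is a generalised least squares calculation with 16 homes × 23 users per measurement time, SD 15, ICC 0.1, compounding loss, a common month-0 mean, period effects and one exposure effect. The restricted set is residents with a month-0 value and at least one follow-up. The within-resident correlation (beyond the home effect) is not in the article, so it is varied as an assumption.

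| Within-resident correlation | SE, all residents | SE, restricted | Variance increase | Power for 5 points, all | Power, restricted |
|---|---|---|---|---|---|
| 0 | 1.77 | 2.00 | 29% | 0.81 | 0.70 |
| 0.2 | 1.61 | 1.81 | 26% | 0.87 | 0.79 |
| 0.3 | 1.53 | 1.70 | 25% | 0.91 | 0.83 |
| 0.5 | 1.32 | 1.46 | 22% | 0.97 | 0.93 |
| 0.7 | 1.04 | 1.14 | 20% | 1.00 | 0.99 |

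As a cruder cross-check, the article's design-effect formula with 16 homes gives power 0.80 at 364 users, 0.71 at 287 and 0.61 at 226. It credits no within-resident correlation either, so it belongs with the first row.

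**4. Does reading baseline as the first available value help?** For a newcomer in the start arm, the first value is taken under the intervention; for a deferred-arm newcomer first measured at 8 months, it is taken under usual care. Adjusting for it would remove part of the effect in one arm. A resident first seen at 16 months would still have no later outcome.

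**The case against.** The strongest reply is that the article nowhere says residents without a month-0 value are excluded, or that the analysis is complete-case. It wants dropouts included, leaves imputation open, names a multilevel model for repeated measurements, and bases the primary outcome on all three measurement times. One could read month 0 as an outcome row already, with the detail left to a fuller document.

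Part of this stands. Exclusion is inferred from how a covariate model works. But considering imputation is not a commitment to it, and the article itself both makes the attrition argument and fixes the adjustment. Those two statements need reconciling whatever another document adds.

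Some stronger readings are tempting and not supported:

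- *Only survivors to 16 months are analysed.* No: residents who leave between 8 and 16 months keep their 8-month value.
- *The trial is underpowered at 0.70.* That holds only at zero within-resident correlation. At 0.3 to 0.7 the restricted set keeps power of 0.83 to 0.99.
- *Residents without a scored drug at month 0 have no baseline APID and are lost too.* The article includes nonusers but does not say how they are scored, so this cannot be concluded.

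It is also fair to say that using newcomers has a price. They are enrolled after allocation, in homes that know their arm, which carries some risk of selection. And under any model, residents gone before 8 months supply only a baseline row.

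**Conclusion.** The conflict is real and should be resolved in the text. As worded, baseline adjustment undercuts the only stated reason for not allowing for 40% loss, does not deliver the intention-to-treat statement for those who leave before 8 months, and departs from the model behind the 1.28 factor. If values are not imputed, about 30% of planned follow-up records do not contribute and the variance of the effect estimate rises by about 20–30%. Whether power falls below 0.80 depends on a correlation the article does not give. The firmer harms are the changed analysis set and the failed attrition argument. These figures assume loss of 30% per year spread evenly over homes, every vacated place refilled, and a single effect common to all exposed periods.

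**What to change.** In Data analysis, replace adjustment for the baseline outcome value as a covariate with a repeated-measures multilevel model in which the 0-, 8- and 16-month values are all outcomes. Include categorical period with a common month-0 mean across arms, exposure terms, and random intercepts for nursing home and for resident within nursing home. Every resident with any measurement then contributes, chance differences at month 0 are still accounted for, and the analysis matches the sample size basis.

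Because newcomers enter unblinded homes after allocation, add a sensitivity analysis restricted to residents present at month 0.

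The cost is about one paragraph of wording, with no extra data or residents. If the baseline covariate is kept without imputation, the attrition argument has to go and the sample size needs an allowance: at 40% loss, 364 / 0.6 = 607 users, and 607 / 0.6 = 1,012 residents.

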In our study, we will integrate PAR with a stepped-wedge cluster RCT to create a PAR-RCT study design. This approach will help us to account for local differences by adapting to local needs, to use a tailored approach to improve local practice, and to create a framework that allows for a degree of generalizability. A cyclic approach of planning, acting, observing, and reflecting will be used [42]. We specifically plan to address two strategies that we assume will increase the intervention’s effectiveness. First, we will provide NHs with tailored information about their perceived problems in managing NPS, including psychotropic drug use, to obtain a match between the problems experienced by NHs and the interventions to be implemented. Second, we will provide NHs with coaching to facilitate implementation. The coach will help to draft and implement the intervention plan, paying close attention to the local context of the NH. This will require dealing with any initial skepticism about non-pharmacological approaches or NH staff concerns in an effort to engender the commitment to change and the active engagement of staff that are essential for successful implementation [40].

We aim to study the effectiveness of implementing a tailored intervention to reduce inappropriate psychotropic drug prescribing in a PAR-RCT. Our goal is to change work practices, processes, and cultures at the level of DSCUs in NHs because these changes tend to have longer lasting effects [43]. Therefore, interventions chosen by the NH staff will not directly target residents, but will instead target medication reviews, behavioral visits, or the provision of information on residents’ life stories. We expect that these psychosocial interventions targeting NH staff can enhance the quality of professional conduct in NH practice, with positive effects for residents. For example, a systematic review demonstrated that studies reporting on cultural change and involving physicians may lead to a substantial reduction of antipsychotic drug prescribing [43]. It is anticipated that our intervention will lead to reductions in inappropriate psychotropic drug prescribing, the frequency of psychotropic drug use, and the frequency of NPS, as well as to an improvement in residents’ QoL. Parallel to the PAR-RCT, a comprehensive process evaluation will be conducted to provide insights into the contribution of the intervention to practice and to identify any barriers to, or facilitators of, implementation.

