^c^The EBPAS + organization culture questionnaires are administered in the context of the problem assessment at 0 months (start intervention group) or 8 months (start deferred intervention group), as well as at 16 months in the context of the process evaluation

Abbreviations: *APID* Appropriateness of Psychotropic Prescription In Dementia, *CMAI* Cohen–Mansfield Agitation Inventory, *CPS* Cognitive Performance Scale, *CVF* Competing Values Framework, *EBPAS* Evidence-Based Practice Attitude Scale, *MPT* Multidisciplinary project team, *NPS* neuropsychiatric symptoms, *NH* Nursing homes, *NPI-NH* Neuropsychiatric Inventory-Nursing Home, *QoL* Quality of Life, *RISE* Revised Index of Social Engagement, *VAS* Visual analog scale

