### Secondary outcomes

The secondary outcomes will be the frequency of psychotropic drug use, the frequency of NPS, and the QoL. The frequency of psychotropic drug use will be extracted by the researchers from medical files, and NPS and QoL will be assessed by nursing staff on paper, in the presence of a researcher. Proxy measures of NPS and QoL (nurse assessments) will be used on the assumption that residents lack capacity. NPS will be measured with the NPI-NH and the Cohen–Mansfield Agitation Inventory (CMAI). QoL will be measured using the visual analog scale (VAS) of the EQ. 5D (i.e., the EQ-VAS).

The NPI-NH measures the prevalence, frequency, severity, and associated caregiver distress of 12 neuropsychiatric symptoms. All symptoms are rated on Likert-type scales, with four-point scales used for frequency, three-point scales used for severity, and six-point scales used for caregiver distress. When a symptom is not present, the frequency, severity, and caregiver distress are not scored [51]. We plan to use the Dutch version of the NPI-NH, which has demonstrated high inter-rater agreement and validity as a rating scale [52].

The CMAI is the most used tool for determining the frequency of agitation and aggression [53]. The CMAI consists of 29 items, subdivided into three subscales: physical aggression, physically nonaggressive behavior, and verbally agitated behavior. Scores are rated on seven-point Likert-type scales, rating symptoms over the preceding 2 weeks from “never” to “several times an hour” [54]. The translated and validated Dutch version by De Jonghe and Kat (1996) will be used, which has established reliability (Cronbach’s α = 0.82) and construct validity (Inter-rater agreement = 0.89) [55–57].

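### The effect models adjust for staff attitude, unit culture and nurse distress, which the intervention can change; attitude and culture have no common pre-randomisation value, and distress is not limited to baseline

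*Protocol article*

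**What the plan says.** The Data analysis section of the protocol article sets one multilevel model for the primary and secondary outcomes. It adjusts for the baseline outcome value, for time, and for confounders that include "type of dementia, distress in nurses due to NPS". It then adds team-level terms: "We will adjust for factors that could explain why an intervention did not succeed at the team level". The examples given are attitude on the EBPAS, and cooperation, working conditions and unit characteristics on the CVF scale. The same section separately plans sensitivity analyses of attitude as an effect modifier.

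Three other places bear on this:

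- **Background.** "Our goal is to change work practices, processes, and cultures at the level of DSCUs in NHs". The coach is also expected to "engender the commitment to change and the active engagement of staff that are essential for successful implementation". A lower frequency of NPS is anticipated.
- **Table 2, footnote c.** EBPAS and CVF belong to the "problem assessment at 0 months (start intervention group) or 8 months (start deferred intervention group), as well as at 16 months".
- **Secondary outcomes.** "The NPI-NH measures the prevalence, frequency, severity, and associated caregiver distress of 12 neuropsychiatric symptoms". NPS is a secondary outcome, and measurements fall at 0, 8 and 16 months.

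**The concern.** Homes are randomised, so the total effect of the intervention does not need adjustment for attitude, culture or distress. If such a variable is measured after the intervention starts and the intervention has moved it, conditioning on it removes the part of the effect that passes through it. Factors chosen because they might explain why an intervention failed describe its mechanism; they are not confounders of a randomised comparison.

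The schedule adds a second difficulty. The only randomised comparison of exposed with unexposed homes is at 8 months. There, start homes have no concurrent EBPAS or CVF value and deferred homes have no 0-month value. What is at stake is the meaning of the primary estimate, its power, and for one way of fitting the model whether an estimate exists at all.

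**Working it through.** **1. The plan's own sample size (Sample size section).** Inputs: difference 5, SD 15, alpha 0.05 (taken as two-sided), power 0.80, 25 residents per home, ICC 0.1.

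- Per arm: 2 × 15² × (1.96 + 0.8416)² / 5² = 141.3, so 142. The total is 284, as stated.
- Stepped-wedge design factor with two steps, one baseline and one later measurement per step: [1 + 0.1 × 74] / [1 + 0.1 × 49] × [3 × 0.9 / (2 × 1.5)] = (8.4 / 5.9) × 0.9 = 1.281. The plan states 1.28.
- 284 × 1.281 = 363.9, so 364. Then 364 / 0.6 = 607. Both agree with the plan.
- Implied standard error: 15 × √(2/142) = 1.78 points.

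**2. Which EBPAS or CVF value could enter the model?**

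| Choice | Start homes | Deferred homes | Consequence |
|---|---|---|---|
| Value at each home's problem assessment | 0 months | 8 months | Calendar time differs by arm; the deferred value comes 8 months after an allocation that staff know |
| 16-month value | after 16 months of intervention | after 8 months of intervention | Post-intervention in every home |
| Visits with a concurrent value only | 0 and 16 | 8 and 16 | Effect not estimable |

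For the last row, the exposure indicator is 0 (start, 0 months), 1 (start, 16 months), 0 (deferred, 8 months) and 1 (deferred, 16 months). That column equals the 16-month indicator. With a separate term for each visit, the design matrix has rank 3 for 4 columns.

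**3. Simulated consequence for a home-level mediator.** Two sequences, three visits, 16 homes of 23 residents, SD 15, ICC 0.1, true total reduction 5 points. The mediator shifts by a constant amount once a home is exposed. Mean estimated reduction over 1,000 runs:

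| Adjustment | 20% mediated | 40% mediated |
|---|---|---|
| None | 4.95 | 5.03 |
| Pre-intervention value (0 or 8 months by arm) | 5.00 | 4.99 |
| 16-month value | 4.98 | 5.04 |
| Concurrent value at every visit | 4.10 | 2.95 |

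A second set (1,500 runs) let the mediator shift grow with duration of exposure, at 40% mediated. The 16-month value then moved the mixed-model estimate from 4.21 to 3.88, and the 8-month arm comparison from 4.98 to 4.58.

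**4. Illustrative power for a concurrent mediator.** Effect left = 5 × (1 − mediated share); power = Φ(effect / 1.78 − 1.96), with the standard error held at its planned value.

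| Assumed mediated share | Effect left | Power |
|---|---|---|
| 0% | 5.0 | 0.80 |
| 20% | 4.0 | 0.61 |
| 30% | 3.5 | 0.50 |
| 40% | 3.0 | 0.39 |

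This can apply to nurse distress, which is available at every NPI-NH assessment. It cannot apply to EBPAS or CVF in the 8-month comparison, because concurrent values do not exist in both arms.

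**5. Nurse distress.** The Data analysis section attaches baseline to the outcome values only. The Sample size section replaces residents who die or leave. For a resident admitted to a home that has already started, even the first distress score is taken after exposure.

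**The case against.** The best reply is that the article never says which measurement enters the model. EBPAS and CVF belong to the problem assessment, which opens each home's own intervention phase, and values taken then cost nothing in the simulation. Distress at baseline is a legitimate covariate. Covariate timing is also a detail that an article commonly leaves to the full protocol or SAP.

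Much of this stands, and it rules out three stronger readings:

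- A reader might infer that part of the effect will certainly be adjusted away. The documents do not support that; it depends on an unstated choice of measurement.
- A reader might apply the power losses to EBPAS and CVF. Those figures need a concurrent mediator and an assumed mediated share.
- A reader might argue that four EBPAS subscales and four CVF types exhaust the degrees of freedom of 16 homes. Nothing says that all of them enter, and CVF is assessed at unit level, with several units possible per home.

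The reply does not remove the point. The adjustment is a stated rule and the EBPAS and CVF schedule is fixed. No later document can supply a common pre-randomisation score that is not collected. Even the harmless choice uses a post-randomisation value in the deferred arm.

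**Conclusion.** The point holds in conditional form. The plan puts into its effect models variables that the intervention aims to change or can change. Two of them have no common pre-randomisation measurement, and the third is not confined to baseline. Depending on the value used, the EBPAS or CVF covariate differs in calendar time by arm, is post-intervention in every home, or leaves the effect inestimable. Any value taken after a home starts can absorb part of the effect.

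The size cannot be derived from the documents. The range of 4.0 to 3.0 points, with power 0.61 to 0.39 against the planned 0.80, assumes a concurrent mediator carrying 20% to 40% of a 5-point effect and an unchanged standard error. It is an illustration, not a forecast. With strictly pre-intervention EBPAS or CVF values the simulated loss is nil.

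**What to change.** State in the analysis plan, before the data are analysed:

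- Remove EBPAS, CVF and any nurse distress value measured after the home started the intervention from the primary and secondary effect models.
- Keep time, the baseline outcome value and pre-exposure resident characteristics such as CPS and type of dementia. Time must stay because exposure rises with calendar time in a stepped-wedge design; cutting the model back to resident characteristics alone would confound the effect with secular trend.
- Say how residents admitted after their home has started are handled, since their first measurements are not pre-exposure.
- Use EBPAS, CVF and post-start distress only in the process evaluation and in exploratory effect-modifier or mediation analyses, labelled as such.

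This deletes model terms, needs no further data and leaves the sample size unchanged, because the calculation contains no covariate adjustment.
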